### **11.2. Study Candidate Screening**

All interested subjects will undergo screening during which their eligibility for the study will be determined.

### **11.3. Informed Consent**

Written informed consent must be obtained from all potential study candidates. Parent or guardian consent is required in patients who are between 7- 18 years old at the time of consent. A subject is considered enrolled only after the subject signs and dates the Informed Consent Form (ICF).

- Subjects and/or subjects' parent/guardian will be asked to sign the Informed Consent form before any study-specific tests or procedures are performed;
- The context of the study must be fully explained and the subjects and/or subjects' parent/guardian must be given the opportunity to ask questions and have those questions answered to their satisfaction;
- Study personnel should explain that even if a subject agrees and/or subjects' parent/guardian agrees to participate in the study and signs an ICF, certain screening procedures might demonstrate that the subject is not eligible to continue participation;
- The Informed Consent form is study-specific and must be approved by the Independent Ethics Committee (IEC) and the sponsor.
- Written informed consent must be recorded appropriately by means of the subject's and/or subjects' parent/guardian dated signature.

### **11.4. Screening Assessments/Procedures (up to 90 days after Informed Consent)**

Enrolled subjects should undergo screening to determine eligibility for participation in the study. Subjects who meet all inclusion criteria (as described in Section 9.2) may be given consideration for participation, provided no exclusion criterion (as described in Section 9.3) is met.

The Written Informed Consent form, screening assessments/procedures, and the Baseline Visit may all be completed on the same day.

Candidate screening assessments/ and or procedures should not take any longer than 90 days from the start of the screening period.

### **11.5. *Baseline: Baseline Visit (up to 7 days; all subjects) & Pocket Adaptor Visit (only PA subjects)***

During the Baseline Visit, a detailed evaluation of subjects' disease state and its impact on their health will be performed. Evaluation of the subjects disease state includes assessment of the type of dystonia (primary, secondary, or idiopathic), and specific diagnoses (e.g. cervical dystonia, blepharospasm, generalized dystonia, focal dystonia etc.) per standard of care at the investigating site. Subjects or the subjects' parent/guardian (for subjects younger than 18 years) will be asked to complete certain evaluations related to their dystonia symptoms, quality of life, mental health status, etc. Subjects' medications for the treatment of dystonia will be documented. It is recommended that genetic testing for DYT status be performed per standard of care.

The Written Informed Consent form may be obtained during the Baseline Visit provided that all screening assessments/procedures are also done on the same day. All baseline evaluations/assessments/ tests must be completed within 7 days of the patient's first baseline visit. Baseline assessments done as part of standard of care screening to determine eligibility for DBS up to 90 days prior to consent may be used for this Baseline Visit (no repetition needed).

#### **11.5.1. Baseline visit (all subjects)**

The following general assessments will be completed during the Baseline Visit. Subjects receiving the Pocket Adaptor will be asked to turn OFF stimulation to obtain their Baseline Visit data. It may take up to 7 days of washout, per investigator discretion, before subjects reached their baseline status with stimulation OFF. The specific assessment or questionnaire delivered to the subject depends on subject classification and age, and guidance regarding these is provided in Table 11-2.

- Medical History
- Concomitant Medications
- Demographic information – Gender, age at consent, level of education, and work/school status.
- Burke-Fahn-Marsden Dystonia Rating Scale (BFMDRS)
- Global Dystonia Rating Scale (GDS)
- Montreal Cognitive Assessment (MoCA)
- Resource Utilization Inventory (RUI) (only for patients without Pocket Adaptor)

- Short Form Health Survey-36 (SF-36 v2) or Short Form Health Survey-10 (SF-10v2) (only for patients without Pocket Adaptor)
- Toronto Western Spasmodic Torticollis Rating Scale (TWSTRS)

Subjects will also be asked about any adverse events since their last study visit (if any).

#### **11.5.2. Pocket Adaptor/Vercise IPG Visit**

Subjects who are going to receive Vercise IPG as a replacement to a non-Boston Scientific IPG, and that may connect the Vercise IPG to components not manufactured by Boston Scientific will have an additional visit at the time of Baseline:

The following assessments, depending on Dystonia type, will be completed with their existing non-BSC system stimulation ON based on status of their non-BSC IPG and subject approval. These assessments may be completed during the Screening Period.

- Burke-Fahn-Marsden Dystonia Rating Scale (BFMDRS)
- Clinical Global Impression of Change (CGI-C)
- Clinical Global Impression of Change – Subject (CGI-C: Sub)
- Clinical Global Impression of Change – Caregiver (CGI-C: Crg) optional
- Global Dystonia Rating Scale (GDS)
- Montreal Cognitive Assessment (MoCA)
- Resource Utilization Inventory (RUI)
- Satisfaction with Treatment Short Form Health Survey-36 (SF-36 v2) or Short Form Health Survey-10 (SF-10v2)
- Toronto Western Spasmodic Torticollis Rating Scale (TWSTRS)

Following completion of assessments, subjects will be scheduled for a Vercise implant.

### **11.6. *Implant Procedure(s) of Vercise System***

Detailed directions for use will be available to each investigator and investigational site in the form of instructional manuals and training by BSC staff. Because DBS is a well-established therapy, neurosurgeons, neurologists, and their staffs have developed their own best procedures and practices for implant, activation, and programming. Standard practices, per local DFUs will be followed for the placement of the Vercise system.

The date of the first lead placement will be considered as Day 0. Alternatively, for subjects receiving BSC IPG and BSC Pocket adaptor as a replacement to non-BSC IPG, the day of BSC IPG implant will be considered as Day 0. Also, if newly marked CE active components- such as the lead or IPG are used, then that day shall be considered as Day 0. All subsequent study schedule visits will occur based on the timing of the Day 0 visit.

Standard practices, per local DFUs will be followed for the placement of the Vercise system.

Post-operative imaging is recommended to be done within 3 months following placement of leads to confirm lead position. A computerized tomography (CT scan) with at least 1.25 mm slice thickness is recommended.

The implant procedure must be performed within 6 months of the baseline.

### ***11.7. Device Activation***

The Vercise system will be activated following completion of the system implant.

Subjects will be asked about any adverse events since their last study visit. Any changes to subjects' medications will be documented.

The device stimulation parameters will be chosen based on subject and physician preference per local site standards/DFU. Subjects or subjects' parent/ guardian will be instructed on the use of the remote control and charging system. Any precautions/restrictions will be discussed.

A monopolar review (optional) capturing efficacy and side effect thresholds will be conducted at this visit to determine initial settings (optional). The final programming parameters (for example, rate, pulse width, etc.) will be documented. Impedance measurements will also be performed and recorded.

Subjects may have as many clinic visits as required for optimization of programming.

### ***11.8. Up to Week 12 ( $\pm 21$ days) Visit***

Several visits following activation of the Vercise system may be made for optimization of therapy and/or management of adverse events. These visits will be scheduled with the neurologist (or neurosurgeon as needed).

Subjects will be asked about any adverse events since their last study visit.

The subjects' device may be checked for performance including an impedance check and programming as needed. The programming parameters and impedances will be documented if required per the local site's standard of care.

### **11.9. *Week 26 ( $\pm 21$ days) Visit***

This visit will be scheduled with the neurologist.

Subjects will be asked about any adverse events since their last study visit. Any changes to subjects' medications will be documented.

The following general assessments must be completed. The specific assessment or questionnaire delivered to the subject depends on subject diagnoses, and guidance regarding these is provided in Table 11-2.

- Burke-Fahn-Marsden Dystonia Rating Scale (BFMDRS)
- Clinical Global Impression of Change (CGI-C)
- Clinical Global Impression of Change – Subject (CGI-C: Sub)
- Clinical Global Impression of Change – Caregiver (CGI-C: Crg) optional
- Global Dystonia Rating Scale (GDS)
- Montreal Cognitive Assessment (MoCA)
- Resource Utilization Inventory (RUI)
- Satisfaction with Treatment (SWT)
- Short Form Health Survey-36 (SF-36 v2) or Short Form Health Survey-10 (SF-10v2)
- Toronto Western Spasmodic Torticollis Rating Scale (TWSTRS)

The subjects' device may be checked for performance including an impedance check and programming as needed. The programming parameters and impedances will be documented, if required per the local site's standard of care.

### **11.10. *Week 52 ( $\pm 56$ days) and Year 2 ( $\pm 56$ days) Visit***

The Week 52 (Year 1) and Year 2 visits will be scheduled with the neurologist.

Subjects will be asked about any adverse events since their last study visit. The following general assessments must be completed. The specific assessment or questionnaire delivered to the subject depends on subject diagnoses, and guidance regarding these is provided in Table 11-2.

- Burke-Fahn-Marsden Dystonia Rating Scale (BFMDRS)
- Clinical Global Impression of Change (CGI-C)
- Clinical Global Impression of Change – Subject (CGI-C: Sub)
- Clinical Global Impression of Change – Caregiver (CGI-C: Crg) optional

- Global Dystonia Rating Scale (GDS)
- Montreal Cognitive Assessment (MoCA)
- Resource Utilization Inventory (RUI)
- Satisfaction with Treatment (SWT)
- Short Form Health Survey-36 (SF-36 v2) or Short Form Health Survey-10 (SF-10v2)
- Toronto Western Spasmodic Torticollis Rating Scale (TWSTRS)

The subjects' device may be checked for performance including an impedance check and programming as needed. The programming parameters and impedances will be documented if required per the local site's standard of care.

#### **11.11. Year 3 ( $\pm$ 56 days) Visit: End of Study Visit**

This visit will be scheduled with the neurologist. Year 3 Visit will be the last study visit.

Subjects will be asked about any adverse events since their last study visit. If anti-dystonic medications were collected during the baseline visit, then any changes to these will be documented. The following general assessments must be completed. The specific assessment or questionnaire delivered to the subject depends on subject diagnoses, and guidance regarding these is provided in Table 11-2.

- Burke-Fahn-Marsden Dystonia Rating Scale (BFMDRS)
- Clinical Global Impression of Change (CGI-C)
- Clinical Global Impression of Change – Subject (CGI-C: Sub)
- Clinical Global Impression of Change – Caregiver (CGI-C: Crg) optional
- Global Dystonia Rating Scale (GDS)
- Montreal Cognitive Assessment (MoCA)
- Resource Utilization Inventory (RUI)
- Satisfaction with Treatment (SWT)
- Short Form Health Survey-36 (SF-36 v2) or Short Form Health Survey-10 (SF-10v2)
- Toronto Western Spasmodic Torticollis Rating Scale (TWSTRS)

The subjects' device may be checked for performance including an impedance check and programming, as needed. The programming parameters and impedances will be documented if required per the local site's standard of care.

#### **11.12.     *Unscheduled Visits***

Unscheduled visits may be made at any time for reasons including reprogramming or for evaluation of a possible adverse event (AE). Each unscheduled visit should be documented with the reason for the visit stated. Details of adverse event must be recorded. If subjects' device was tested or programmed, the final programming parameters and impedances will be documented.

#### **11.13.     *Revisions/Replacement of Leads or IPG***

It is possible that leads may be placed incorrectly, migrate, fail or get infected. This may require repositioning, replacement or explant. It is also possible that the IPG may fail and require replacement or explant, or need repositioning due to migration, discomfort, etc. Any replacements, revisions or explants performed during the course of the study should be documented.

#### **11.14.     *Study Completion***

De-novo subjects will be followed for 3 years after first lead implant, and subjects with Pocket Adaptor will be followed for 3 years post Vercise IPG placement. The study will be considered complete once all subjects have completed Year 3 Visit.

#### **11.15.     *Source Documents***

Where copies of the original source document as well as printouts of original electronic source documents are retained, these shall be signed and dated by a member of the investigation center team with a statement that it is a true reproduction of the original source document.

All source documentation (Table 11-3) will be retained at the investigational site. The type of the source documentation will be specific for each study visit and whether the visit was conducted at the neurologist's or a neurosurgeon's office. When neurologist and neurosurgeons are not at the same institution, each office will be responsible for keeping source documentation related to only those study visits conducted at their institution. Examples of source documents include, but are not limited to the following:

- Informed consent form and consent process documentation;
- Documentation of medical history components;
- Medical records from clinical visits (i.e. progress notes, etc.) and operative procedures (i.e. Operative Report, etc.);
- Study-specific source document worksheets (if applicable);

- Laboratory/Test Results, if applicable;
- Neuropsychological and psychiatric tests results;
- Questionnaires such as SF-36v2, etc.;
- Programming information from Clinician Programmer following programming/testing.
- Imaging (i.e. pre-procedure CT scan and/or MRI, post-OP CT scan of lead position).

**Table 11-3: Source Documentation Requirements**

| Requirement                           | Disposition                      |
|----------------------------------------------|-----------------------------------------|
| Informed Consent Form                        | Retained at investigational site |
| Consent Process Documentation                | Retained at investigational site |
| Inclusion & Exclusion Criteria Documentation | Retained at investigational site |
| Medical Records                              | Retained at investigational site |
| Patient Questionnaires                       | Retained at Investigational site |
| Laboratory/Test Results (if applicable)      | Retained at investigational site |
| Imaging films/prints (if applicable)         | Retained at investigational site |
| Technical Source Form                        | Retained at investigational site |
| Clinician Questionnaires                     | Retained at investigational site |

## **12. Statistical Considerations**

### **12.1. *Analysis of Clinical Endpoints***

A number of clinical endpoints are included in this study, as described in Section 7. Subjects in this study will be diagnosed for primary or secondary dystonia, and will be assigned to either of the two subgroups. All clinical endpoints will be evaluated separately for these two subgroups, and will be summarized using descriptive statistics for continuous variables (e.g., mean, standard deviation, N, minimum, maximum) and frequency tables or proportions for discrete variables. Estimates of all endpoints will be reported, as well as the 95% confidence intervals.

### 12.1.1. Responder Rate

A responder is defined as a subject with 30% or greater reduction in Baseline BFMDRS or TWSTRS score in non-cervical and cervical dystonia subjects, respectively. The responder rate is calculated as the number of responders divided by the number of subjects within each subgroup. Because the number of responders follows a binomial distribution, the 95% confidence interval for the proportion of responders will be calculated using the Clopper-Pearson method.

### 12.1.2. Sample Size

The sample size is calculated as the number of subjects needed to achieve a specific target precision for the responder rate. The goal is to obtain an estimate of the responder rate while limiting the uncertainty surrounding that estimate. The precision of the responder rate is measured by the width of its 95% confidence interval, with larger widths indicating lack of precision. The study is designed such that the difference between the upper and lower 95% confidence bounds for the responder rate is, with 95% certainty, less than the pre-specified target. That is, given the sample size parameters; there is a 95% chance that the target precision for the primary endpoint will be achieved.

Due to different prevalence of primary and secondary dystonia, the sample size calculation is based on the subgroup with the lower prevalence in the study population. This is the secondary dystonia group.

Parameters for the sample size calculations (where N is the total number of implanted subjects) are shown in Table 12.1.

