### **4.3. *Factors affecting DBS treatment in dystonia patients***

Improvement in DBS treatment for dystonia is variable from one patient to another, and could depend on factors related to the disease state or treatment. A number of studies have focused on understanding factors that could possibly have predictive value on the magnitude of improvement with DBS treatment for dystonia. These factors include dystonia etiology, and duration of disease. A recent study also showed higher volume of activation of GPi in highly improved patients compared to less improved patients.

As mentioned earlier, primary dystonia is idiopathic in nature, whereas secondary dystonia results from apparent outside factors and can be attributed to a specific cause. A group of early-onset primary dystonia syndromes can be classified based on clinical presentation and assigned to a DYT number. At present about 20 monogenetic dystonia syndromes, include seven primary dystonia syndromes (DYT1, 2, 4, 6, 7, 13, and 17) have been classified. Of these dystonia syndromes, the genes TOR1A (causing DYT1), and THAP (DYT6) have been identified. Primary dystonia patients, specifically with DYT1 positive mutation have been typically shown to have better outcomes as compared to secondary dystonia patients (Borggraefe et al., 2012, Egidi et al., 2007, Krause et al., 2004, Markun et al. 2007, Lumsden et al, 2013). Treatment outcome in secondary dystonia patients has been quite poor (Krause et al., 2004; Pretto et al., 2008; Vidailhet et al., 2009), with the exception of drug-induced secondary dystonia patients who seem to benefit significantly from DBS treatment (Egidi et al., 2007). Considering the variability in treatment effect, a subgroup analysis between primary and secondary dystonia patients will be performed. Further exploratory analysis in other primary monogenetic dystonia syndrome population is also intended.

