### ***10.4. Enrollment Controls***

Enrollment will remain open until one of the following events occurs:

- 200 subjects are implanted.

- The study is terminated at any time, at the Sponsor's discretion.

Enrollment controls will be implemented per the Enrollment Communication Plan developed for this study.

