**Table 12.1: Sample Size Parameters**

|                                                     |                     |
|-----------------------------------------------------|---------------------|
| Significance level ( $\alpha$ )                     | 0.05                |
| Assumed responder rate ( $\pi$ )                    | 0.15                |
| Target width of $1-\alpha$ confidence interval (CI) | 0.30                |
| Probability of achieving target CI width            | 0.95                |
| Subgroup prevalence                                 | 0.25                |
| Attrition (%)                                       | 30                  |
| Total N (both subgroups)                     | 200 Subjects |

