#### **12.3.1. Interim Analyses**

The two subgroups in the study (primary dystonia and secondary dystonia) will be tested separately and no pooling across subgroups will be performed. Consequently, analysis will proceed when sufficient power is reached separately for each subgroup.

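### With the planned Clopper-Pearson interval, 200 implants give about a 93% chance, not 95%, of a confidence interval narrower than 0.30 for secondary dystonia, with no allowance for a varying subgroup size

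*Protocol*

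**What the plan says.** Section 12.1.2 sizes the registry on precision. Success means that the upper minus the lower 95% confidence bound for the responder rate is below a set target, and the section concludes that, given the parameters, "there is a 95% chance that the target precision for the primary endpoint will be achieved". The sizing rests on the less common subgroup, secondary dystonia.

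Table 12.1 and the synopsis give the inputs: alpha 0.05, responder rate 0.15, target width 0.30, prevalence 0.25, attrition 30%, total N 200, and 0.95 for "Probability of achieving target CI width". The synopsis describes the 0.25 as a minimum; Table 12.1 does not.

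Section 12.1.1 fixes the analysis: "the 95% confidence interval for the proportion of responders will be calculated using the Clopper-Pearson method".

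Under section 10.4, enrollment closes when "200 subjects are implanted" or when the sponsor terminates the study. No number of places is set for either subgroup. Section 12.3.1 states that "analysis will proceed when sufficient power is reached separately for each subgroup".

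**The concern.** The 95% probability is the only quantitative justification for N = 200, so it should follow from the inputs printed beside it and from the interval that will be reported. Two things suggested that it might not. Clopper-Pearson intervals are wider than the Wald or score intervals often used in sizing. And the step from 200 implants to 35 evaluable subjects uses expected values, although neither the subgroup count nor the dropout count is under control.

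Section 12.3.1 adds a related problem: it ties the timing of analysis to power, but the design states no hypothesis, effect size or power.

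At stake is whether a reader can rely on the stated precision for the smaller subgroup, and whether the time of its analysis is settled in advance.

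**Working it through.** **Inputs.** Table 12.1: π = 0.15, alpha = 0.05, target width 0.30, prevalence 0.25, attrition 30%, N = 200 implanted. Section 12.1.1: Clopper-Pearson.

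**Step 1. Evaluable secondary-dystonia subjects.** 200 × 0.25 = 50 implanted; 50 × 0.70 = 35 evaluable.

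**Step 2. Interval width by number of responders x, n = 35.** The lower bound is the 0.025 quantile of Beta(x, n − x + 1); the upper bound is the 0.975 quantile of Beta(x + 1, n − x).

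| x | lower | upper | width |
|---|---|---|---|
| 7 | 0.084 | 0.369 | 0.285 |
| 8 | 0.104 | 0.401 | 0.297 |
| 9 | 0.125 | 0.433 | 0.308 |
| 10 | 0.146 | 0.463 | 0.317 |

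The width is below 0.30 for x ≤ 8. (It is also narrow when nearly all subjects respond, but at π = 0.15 that has negligible probability.)

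**Step 3. Probability of meeting the target.** P(X ≤ 8 | n = 35, π = 0.15) = 0.931. The stated value is 0.95; the gap is 1.9 points. For a width below 0.31 the condition becomes x ≤ 9, and P(X ≤ 9) = 0.971.

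**Step 4. Evaluable n needed for a strict 95%.** n = 35 gives 0.931, n = 36 gives 0.920 and n = 37 gives 0.958. The probability does not rise steadily because the number of responders allowed moves in whole steps. So n = 37; 37 / 0.70 rounds up to 53 secondary implants; 53 / 0.25 = 212 implants in total, 6% above 200.

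**Step 5. Where 200 might come from.** The protocol gives neither the interval nor the attrition formula used in sizing, so these are possibilities only.
- Wald: 33 evaluable subjects suffice, so N is 189 to 192. At n = 35 the probability is 0.989.
- Wilson, Agresti-Coull or Jeffreys: 31 suffice, so N is 178 to 180. At n = 35 the probability is 0.996.
- Clopper-Pearson with attrition added as n × (1 + 0.30): 37 × 1.3 = 48.1, rounded up to 49, and 49 / 0.25 = 196. This is close to 200, but losing 30% of 49 leaves about 34, where the probability is 0.873.

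**Step 6. Sensitivity to chance variation in n.** Assume that each implanted subject is independently secondary and evaluable with probability 0.25 × 0.70 = 0.175, and average the step 3 probability over n ~ Binomial(200, 0.175).
- Both counts random: 0.857.
- Exactly 50 secondary implants, attrition random, n ~ Binomial(50, 0.70): 0.889.
- Prevalence 0.27, attrition 30%: 0.958 with n fixed at 37 (37.8 rounded down); 0.918 with n random.
- Prevalence 0.30, attrition 30%: 0.999 with n fixed at 42; 0.971 with n random.

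**Step 7. The trigger in section 12.3.1.** The synopsis and section 12.1 describe descriptive summaries with confidence intervals, and section 12.1.2 sizes on interval width. No null value, alternative or power is given for either subgroup, so there is no point at which the condition in section 12.3.1 could be judged to be met.

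**The case against.** **The gap is small.** It is 1.9 points, and 9 responders instead of 8 miss the target by only 0.008. This stands, and it limits the severity.

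**Another interval may have been used for sizing.** Wald or score intervals exceed 95% at n = 35, and section 12.1.2 names none. But section 12.1.1 commits to Clopper-Pearson, and the claim concerns the interval that will be reported. Sizing on a narrower interval would explain the figure without making it correct.

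**The denominator could be all implanted subjects.** Section 12.1.1 divides by the subjects in the subgroup, and the intent-to-treat set contains everyone implanted. With n = 50 the probability is about 1.00. But the 30% attrition row in Table 12.1 would then do nothing. The table as printed implies 35; if 50 is meant, the table needs correcting in another way.

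**The claim is conditional on its parameters.** This stands against a stronger reading. A reader might infer that the protocol promises 95% and delivers 86%. The documents do not support that: section 12.1.2 makes no claim about a random subgroup count, and the 86% takes as exact a prevalence that the synopsis calls a minimum. Somewhat higher prevalence removes the shortfall.

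**The responder rate might be higher.** Section 4.3 notes poor outcomes in secondary dystonia, "with the exception of drug-induced secondary dystonia patients who seem to benefit significantly from DBS treatment", and such patients are not excluded. A reader might conclude that 0.15 is wrong. Section 4.3 gives no responder rate for any subgroup, and its general statement supports a low planning value. A higher rate would widen the interval, but it departs from the assumption and is not an error in the calculation.

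**Section 12.3.1 might be read as stopping once the interval is narrow enough**, which could bias the estimate. The protocol does not say so. The supported criticism is that the trigger is undefined.

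**Conclusion.** The stated 95% is slightly too high. On the protocol's own inputs and planned interval it is about 93% for a width below 0.30; a strict 95% needs 37 evaluable secondary-dystonia subjects, or 212 implants. This rests on 35 evaluable subjects as the denominator, which is what the attrition row implies, and on a true rate of 0.15.

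Separately, the calculation allows for no chance variation in subgroup size or dropout. The resulting 86% (89% with only attrition random) is a sensitivity result at exactly 0.25 prevalence and 30% attrition with independent subjects. It shows how little margin there is; it does not contradict what the protocol claims.

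The power-based trigger in section 12.3.1 has no meaning in this design.

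The whole is a minor-to-moderate correction. The registry is descriptive, no success criterion depends on the 0.30 width, and the observed interval can be reported whatever its width.

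**What to change.** 1. **Section 12.1.2, Table 12.1 and the synopsis.** Restate the probability as about 93% for a width below 0.30 with 35 evaluable subjects. Alternatively, keep the 95% requirement by setting the target width at 0.31, which gives 97%. State that the figure uses Clopper-Pearson.
2. **Same places.** Add the 86%, labelled as a sensitivity result for a width below 0.30 when subgroup size and attrition vary at 0.25 prevalence and 30% attrition.
3. **Section 12.3.1.** Replace the power condition with a trigger that does not depend on the outcome data: a subgroup is analysed for a visit once all its implanted subjects have passed that visit window or left the study.

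The cost is protocol wording and a slightly less favourable stated figure. No subjects are added. A cap on primary-dystonia implants is not recommended: it would restrict a registry that section 12.2.2 intends to enroll consecutively, and it would make the 86% obsolete.
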